##### Analysis of associated factors to the main criteria

Factors associated with being a severe case (using paper or e-IMCI and using PO or not) among IMCI outpatients, being hospitalized among severe cases, non-referral among severe cases will be studied using a multivariate logistic regression, adjusting for clustered variables (PHC, support of IMCI paper or electronic, rural/urban location), and for individual data (age, sex, socio-demographics, IMCI classification illness, comorbidities, seasonality, distance from home to PHC or district hospital, SpO2 level threshold using PO,...), using robust standard error to take into account the cluster effect within each PHC. All *P* values will be two-sided, with P values < 0.05 considered statistically significant.Kaplan-Meier estimates of the cumulative probability of oxygen therapy delivery and Day-14 survival will be performed for all identified severe cases with hypoxemia, whether hospitalized or not. Day-14 mortality associated factors will be analyzed using logistic regression. Additionally, in a sensitivity analysis missing data will be handled by using a complete data analysis and will consider the maximum bias hypothesis replacing missing data or dropouts by death values.The pathways (hospital transfer) and patterns of care (access to oxygen therapy, volume, duration) will be analyzed and their correlates investigated using a logistic regression.

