The WHO generic guidelines for IMCI were provided in 2005, then revised in 2014 specifically for pneumonia [29, 30, 34] and were revised for neonates in 2019 [35]. At each PHC, the AIRE project will be conducted with their current national guidelines that present few specificities according to the adaptation of the WHO guidelines. In addition, there will be also a distinction between the countries using paper IMCI support (Niger, Guinea and Mali - Dioila health district) and those using electronic IMCI (e-IMCI). Indeed, Terre des hommes (Tdh) NGO has developed the Integrated electronic Diagnosis Approach (IeDA) [36] in Burkina Faso and Mali - Markala health district. It is a digitalized IMCI algorithm via Commcare software used by HCW to perform IMCI consultations on an electronic consultation register via a tablet.

In all AIRE PHCs, HCW will diagnose and treat the child according to paper or electronic-based IMCI guidelines and incorporate the operational use of PO only after the child’s examination and IMCI classification (Fig. 2), given the International Advisory Group recommendation (composed by WHO, Unitaid, Unicef, and expert representatives). The PO will be used among the following eligible children according to the IMCI classification and according to age and signs:0–59 days: all sick children2–59 months, with cough and difficulty breathing: all sick children (green, yellow or red cases classified by IMCI)2–59 months, without cough or difficulty breathing: those classified as yellow or red.

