#### Outcomes evaluation

A population-based cross-sectional study of all children under 5 years of age managed will be conducted in the 16 research PHC implementing the integration of PO into IMCI (electronic or paper) to assess: pathways, patterns, costs of care. A prospective longitudinal follow-up of severe cases until Day-14 after the index IMCI-consultation will document their health outcomes.

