#### Outcomes evaluation

Cross-sectional study of pathways and patterns of care will be conducted among all IMCI children eligible for PO use with caregiver consent by research PHC. Children will be recruited consecutively during the 12-month.

Direct and indirect costs will be collected for a representative sub-sample of two categories of children: IMCI outpatients (green and yellow cases) and severe cases requiring hospital transfer (5 per category per PHC per month, i.e. 1920 children in total).

Day-14 health outcome will be collected only for severe cases. To assess the child mortality on Day-14 of all severe cases identified with an accuracy of plus or minus 3% per country and adding 10% lost to follow-up, we aimed to recruit at least 710 severe cases aged 2 to 23 months (mortality estimated at 10%) and 375 children aged between 24 and 59 months (mortality estimated at 5%), i.e. 1085 children between 2 and 59 months old per country over 12 months, for a total of 4340 children. We will only describe mortality in neonates (aged less than 59 days) enrolling them all over the 12 months of the operational study with a maximum of 400 per country. Overall, we will follow a maximum of 1485 children per country, i.e. a maximum of 5940 severe cases over the study period, representing approximately 15% of the total IMCI population which will be a total of 40,000 children expected for the four countries.

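### The severe-case model is described as covering IMCI outpatients, but non-respiratory children aged 2–59 months enter only if yellow or red, so contrasts across the eligibility strata are partly made by the entry rule

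*Protocol article*

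**What the plan says.** The entry rule is in the Background, The AIRE operational intervention strategy, Step 2. For the youngest group it is "0–59 days: all sick children". For children aged 2–59 months with cough or difficulty breathing it is "all sick children (green, yellow or red cases classified by IMCI". For the rest it is "2–59 months, without cough or difficulty breathing: those classified as yellow or red". The section on study population and inclusion at research sites repeats the exclusion of non-respiratory green children aged 2–59 months and enrols only eligible children with caregiver consent. The abstract agrees, and so does Sample size, Outcomes evaluation, where the cross-sectional study "will be conducted among all IMCI children eligible for PO use with caregiver consent by research PHC".

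Two places describe a wider population. The AIRE study design, Outcomes evaluation, announces "A population-based cross-sectional study of all children under 5 years of age managed will be conducted in the 16 research PHC". Data analysis, under the heading on factors associated with the main criteria, plans a multivariable logistic regression of "Factors associated with being a severe case (using paper or e-IMCI and using PO or not) among IMCI outpatients", adjusting among other things "for individual data (age, sex, socio-demographics, IMCI classification illness, comorbidities, seasonality" and further items.

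**The concern.** IMCI colour helps to decide both who enters the dataset and who counts as severe. The children left out are green and receive no PO measurement, so under the plan's own definition they could only have been counted as non-severe. They are missing from one stratum alone, and that stratum is defined by age group and illness type, which are what the model is meant to study.

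This is selection on the outcome that differs by exposure. It biases odds ratios as well as proportions. Putting age and illness type in the model does not repair it, because the absent children are absent by outcome category within a stratum. A reader of the fitted model would see non-respiratory illness, and age above 2 months, associated with severity even if true risk were equal everywhere.

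**Working it through.** **Inputs.** The entry rule and the covariates are as quoted above. The severe share comes from Sample size, Outcomes evaluation: 4 × (710 + 375 + 400) = 5,940 severe cases at most, and 5,940/40,000 = 14.85%, which agrees with the stated figure of approximately 15%. It is a follow-up maximum set against an expected total, so it serves here only as a convenient value. The proportion of green children is given nowhere and is assumed over a range.

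**Comparison groups under the entry rule**

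| Stratum | Non-severe children available |
|---|---|
| 0–59 days | green and yellow |
| 2–59 months, respiratory | green and yellow |
| 2–59 months, non-respiratory | yellow only |

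**Formula.** Let g be the green share of the non-severe children in the third stratum. Removing them leaves the number severe unchanged and multiplies the number non-severe by (1−g). The observed odds of severity are then the true odds × 1/(1−g).

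**Illustration at 2–59 months.** Assume that respiratory and non-respiratory children have the same true mix, with 150 severe per 1,000. The true odds ratio is then 1. Respiratory odds are 150/850.

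- 20% of all children green (g = 20/85 = 0.24): (150/650)/(150/850) = 850/650 = 1.31.
- 40% green (g = 40/85 = 0.47): (150/450)/(150/850) = 850/450 = 1.89.
- 60% green (g = 60/85 = 0.71): (150/250)/(150/850) = 850/250 = 3.40.

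**Adjusted model.** A main-effects logistic regression was fitted to expected counts, with 15% severe in every cell, 10% of children under 2 months and half respiratory (both assumed). With all IMCI children included, both odds ratios are 1.00. With the entry rule applied:

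| g | 1/(1−g) | OR, under 2 months | OR, respiratory | Apparent severe share, 2–59 months non-respiratory |
|---|---|---|---|---|
| 10% | 1.11 | 0.95 | 0.91 | 16.4% |
| 25% | 1.33 | 0.86 | 0.77 | 19.0% |
| 50% | 2.00 | 0.69 | 0.54 | 26.1% |
| 75% | 4.00 | 0.45 | 0.29 | 41.4% |

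Adjustment does not bring either odds ratio back to 1. The direction is the same throughout: non-respiratory children aged 2–59 months look more severe than they are. Only the size depends on g.

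**Reach.** The missing children all lie above 2 months, so the age distortion appears mainly at that boundary. Within 2–59 months it arises only if the green share among non-respiratory children changes with age. The models of hospitalisation and non-referral are fitted among severe cases, none of whom is removed by this rule.

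**The case against.** The best reply is that the population is already defined. The abstract, the inclusion section, the sample size section, the outcome objectives and the opening item of the descriptive analysis all speak of PO-eligible children, so the wider wording in the model description may be shorthand. Among PO-eligible children the odds ratios are arithmetically valid descriptions. That much stands. It does not settle the matter, because relabelling leaves the comparison group different across strata: age and illness-type contrasts would still partly restate eligibility.

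A second reply is that the article does not commit to a single pooled fit, and that stratification or interaction terms may be set out in a fuller document. This is fair as to what is unknown. It is not the basis of the point, which is that the model as stated names the wrong population and includes covariates that define the entry strata.

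Several stronger readings are tempting, and the documents do not support them:

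- A reader might infer that the severe prevalence over all consultations will be overstated. It will not: Data collection and Data analysis, Context evaluation, take it from monthly aggregate counts over all IMCI consultations, by age group and sex.
- A reader might infer that an odds ratio such as 1.89 is one the plan will report. The covariate list has IMCI illness classification; the respiratory/non-respiratory label appears in the descriptive list. The two overlap but are not the same variable.
- A reader might infer that the project's question of for whom PO works is undermined. The specific objectives assign that question to the realist evaluation, not to these odds ratios.

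**Conclusion.** The point holds for the severe-case model. As stated, it would give associations with illness type, and with age across 2 months, that are partly created by eligibility. The direction follows from the entry rule. The size is not known: under the assumptions of equal true severity, 15% severe and 20–60% of all children green, the false non-respiratory versus respiratory odds ratio is 1.31–3.40. If few non-respiratory children are green the effect is small; at g = 10% the adjusted odds ratios are 0.95 (under 2 months) and 0.91 (respiratory).

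The documents do not support extending this to age effects generally, to the analyses among severe cases, or to the aggregate prevalence figures. The stated limitation on generalisation in the Discussion concerns the choice of health centres and does not cover it.

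**What to change.** 1. In The AIRE study design, Outcomes evaluation, and in the description of the severe-case model, state the population as PO-eligible children with consent.
2. Fit and report the severe-case model separately in the three eligibility strata: 0–59 days; 2–59 months respiratory; 2–59 months non-respiratory. State that in the last stratum the non-severe group is yellow only.
3. Do not interpret odds ratios for age across 2 months, or for respiratory versus non-respiratory illness, from a pooled model as correlates of severity among all IMCI outpatients.
4. As a secondary analysis only, compare these factors across strata in children whose clinical IMCI colour before PO was yellow or red. Label it as severity given at least yellow, and note that it omits green children reclassified by PO. It answers a different question and cannot replace step 2.
5. Keep the aggregate data as the source for severe prevalence over all consultations, as already planned. They cannot repair the individual-level regression.

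No new data are needed. The cost is a change of analysis wording and somewhat wider intervals, since each stratum uses fewer children.

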### Objectives of the AIRE research protocol

The main objective of the AIRE operational research protocol is to evaluate the process of systematic use of PO (with hospital referral if hypoxemia is diagnosed with SpO2 < 90%, or if children is classified as a red case using the clinical IMCI classification based on paper or electronic support) during the IMCI consultation in children under 5 years old at primary health centers (PHC) in four West African countries. This research protocol will include three complementary components: a) evaluation of the context (infrastructure, personnel, use of PO, characteristics of IMCI’s outpatients), b) process evaluation (acceptability, fidelity, implementation challenges, realist evaluation) and c) outcome evaluation (care pathways, patterns of care, costs of care, and day-14 health outcomes for severe cases). These three components are based on the Donabedian model (context, process, outcome) often used to assess the quality of care [37].

Overall, the AIRE project will provide research evidence, using mixed quantitative and qualitative methods to answer the following questions measured in field conditions of PO use at the PHC level: why and how routine PO use into IMCI works (or not), for whom, in what contexts and with what results? In each component, we will specifically explore the differences when using e-IMCI vs paper-based IMCI. This will allow a better understanding of the strengths, weaknesses, opportunities and threats of the PO intervention as a whole, and the action levers for an optimized scaling up of the PO implementation at the country level.

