#### Specific objectives of the evaluation of the PO implementation

The assessment of the context aims to describe at baseline and over the study period all the AIRE sites introducing PO: health infrastructures, nursing staff, frequency of use of PO and characteristics of IMCI outpatients.Process evaluation aims to:Assess the level of acceptability of the innovation (PO) introduced by the project among health workers and caregivers.Describe the fidelity of the implementation, i.e. to what extent the final implementation is in line with the planned activities of the AIRE project (check whether the activities planned by the project have actually been implemented, and also often and for as long as originally planned).Analyze how the implementation of the AIRE project is organized, what are its challenges, what are the factors that influence it (including e-IMCI vs paper-IMCI).Understand how the AIRE project works, for whom, in which specific contexts and why, using a realist evaluation.The outcomes evaluation in research sites aims to:Describe the characteristics of eligible children for PO use during the IMCI consultation, their classification using IMCI alone, then using IMCI and PO, comparing their effect on hospital referral decision.Evaluate the care pathways from the first symptoms, and their correlates for IMCI outpatients and for all severe cases of any etiology (non-respiratory and respiratory) identified at the PHC level. This will include the added value of using PO for e-IMCI guidelines versus paper-IMCI guidelines.Evaluate the patterns of care (use of PO, oxygen therapy, medications, exams) and their associated factors for both IMCI outpatients and for all severe cases of any etiology (non-respiratory and respiratory) identified at the PHC level.Assess the frequency and correlates of successful transfer to hospital of severe cases and the reasons for missed opportunities.Measure the direct costs (medical and non-medical, including hospital transfer for severe cases) and indirect costs from a societal and health system perspective for managed cases (severe and non-severe), including the deployment of PO.Assess the health outcome on day-14 after the index consultation (death, alive still under care, alive cured, lost to follow-up) and correlates for all severe cases.

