## Discussion

AIRE research protocol will provide useful and original information on the introduction of routine PO use into IMCI consultations at PHC level by addressing several West African specificities compared to other regions of sub-Saharan Africa:Children mortality rates in West Africa are among the highest in sub-Saharan Africa and strongly correlated with indicators of poverty, underlying malnutrition and infectious diseases [58–60]. The disease burden is complex. Fever-related illnesses remain one of the leading causes of death in children under 5, including malaria and pneumonia. Malaria is particularly acute in West Africa [61] with prevalence ranging between 30 and 64%. Sickle cell disease is also widespread and is an invisible and underestimated cause of anemia and a neglected cause of morbidity in children under-5 in West Africa [62, 63]. This adds to the context of malnutrition often coupled with specific nutritional deficiencies (lack of iron [64], folates and other micro-nutrients) and the presence of other parasites (especially helminths) playing an underestimated role in “chronic epidemic anemia” [65], which is an underlying factor associated with almost half of deaths of children under-5 in West Africa. Second, all these comorbidities including hypoxemia are frequently neither identified nor treated contributing synergistically to the fatal worsening of severe cases among children in West Africa.The West African health system is also weak with insufficient health resources, low access to health services and insufficient investment in frontline health care. There is a critical shortage of health workers, particularly at the primary health care level and in poor rural areas. As training programs progress, qualified personnel often leave to work elsewhere [66]. This leads to issues of health equity, where there are currently many underserved children and often inadequate quality of care [66, 67]. Inadequate clinical capacity (i.e. inadequate implementation of IMCI guidelines) to identify severe cases in neonates and children means that children with danger signs or signs not specific and with severe illness (including malaria, pneumonia, and other infectious diseases) are missed or misdiagnosed at PHC level and not referred to hospital [67]. In the context of the COVID-19 pandemic, the West African health system has been further disrupted, with an expected indirect impact on both delivery and demand for routine IMCI care among children under-5 that needs to be better described and understood [68].Finally, the cost of care could impact access to care in West Africa: health care for children under-5 is free for families in Niger and Burkina Faso but not in Mali and Guinea except for malaria, tuberculosis, HIV and malnutrition. However, the user fee abolition policy is currently facing a major obstacle such as the sustainability of financing which impacted the cost of care [69]. As it is standard practice to ask families to pay for care at the point of service, the capacity to pay is a major determinant of access to care, particularly for hospital referral creating major social inequities [70]. Generally, urban versus rural populations, and those with higher socio-economic status (SES) and education are more likely to seek care with health providers than lower SES groups or illiterate population. For example, the 2012 Demographic Health Survey in Mali reported that among children who experienced fever in the 2 weeks preceding the survey, 43% of urban populations sought care from a health provider, versus only 29% in rural areas [71].

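### In the logistic models for associated factors, listing health centre (PHC) as a covariate removes the e-IMCI versus paper main effect; without it, the contrast is inseparable from one NGO and, outside Mali, from country

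*Protocol article*

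**What the plan says.** The protocol article, under Analysis of associated factors to the main criteria, sets multivariate logistic models for being a severe case, being hospitalized and non-referral. It describes them as "adjusting for clustered variables (PHC, support of IMCI paper or electronic, rural/urban location"), plus individual covariates, "using robust standard error to take into account the cluster effect within each PHC". Significance is set there too: "values will be two-sided, with P values < 0.05 considered statistically significant".

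The section on the AIRE operational intervention strategy separates the "countries using paper IMCI support (Niger, Guinea and Mali - Dioila health district) and those using electronic IMCI (e-IMCI"); the electronic sites are Burkina Faso and Mali's Markala district. Table 1 gives support, implementing NGO and PHC numbers by district.

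The format comparison is a stated aim: "In each component, we will specifically explore the differences when using e-IMCI vs paper-based IMCI". The specific objectives say of the care-pathway objective: "This will include the added value of using PO for e-IMCI guidelines versus paper-IMCI guidelines". The cost analysis speaks of investigating the effect of the support used. The closing Discussion names two limits, the absence of a comparison group and the selection of PHCs. It does not mention that format is tied to NGO and country.

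**The concern.** Two separate problems meet in this comparison.

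- **Identification.** A factor that never varies inside a PHC has no main effect left to estimate once each PHC has its own fixed term. Software will then drop the format column, the rural/urban column or an arbitrary PHC indicator. Any odds ratio still printed for format would depend on which column was dropped.
- **Confounding.** Format was not allocated across PHCs. It follows the district, and with it the implementing NGO and mostly the country. A coefficient obtained without PHC terms would therefore carry differences between NGOs and countries.

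At stake is the reading of results offered to national decision-makers. A difference between countries or implementers could be reported, with a P value, as an effect of e-IMCI.

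**Working it through.** **Inputs.** Table 1, research PHCs by district:

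| District (country) | Research PHCs | Format | NGO |
|---|---|---|---|
| Dedougou (Burkina Faso) | 2 | electronic | Terre des hommes |
| Boromo (Burkina Faso) | 2 | electronic | Terre des hommes |
| Matoto (Guinea) | 0 | paper | ALIMA |
| Telimele (Guinea) | 4 | paper | ALIMA |
| Dioila (Mali) | 2 | paper | ALIMA |
| Markala (Mali) | 2 | electronic | Terre des hommes |
| Niamey IV (Niger) | 2 | paper | Solthis |
| Dosso (Niger) | 2 | paper | Solthis |

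**Reproducing the plan's totals.** Research PHCs: 2+2+0+4+2+2+2+2 = 16. Operational PHCs: 49+38+16+15+25+19+10+30 = 202. Both agree with Table 1. Electronic research PHCs: 2+2+2 = 6; paper: 4+2+2+2 = 10.

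**Step 1: PHC as a fixed covariate.** The e-IMCI indicator equals the sum of the indicators of the six electronic PHCs, so it lies in the space that the PHC terms already span. Rural/urban location is a property of the PHC and is absorbed in the same way.

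**Step 2: rank of the PHC-level design matrix, intercept included.**

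| Terms | Rank without e-IMCI | Rank with e-IMCI | e-IMCI main effect |
|---|---|---|---|
| PHC | 16 | 16 | not identified |
| District | 7 | 7 | not identified |
| NGO | 3 | 3 | not identified |
| Country + NGO | 5 | 5 | not identified |
| Country | 4 | 5 | identified |

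**Step 3: how much of format is country.** Over 16 PHCs the mean of e-IMCI is 6/16. Total sum of squares = 16 × (6/16) × (10/16) = 3.75. Within country, Burkina Faso, Guinea and Niger contribute 0. Mali (2 of 4 electronic) contributes 4 × 0.5² = 1.00. So R² on country = 1 − 1.00/3.75 = 0.733. After country adjustment, only four PHCs carry information on format: Markala 2 and Dioila 2. Those two districts also differ in NGO.

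**Step 4: precision of the Mali contrast.** Four clusters in two groups leave about 4 − 2 = 2 cluster-level degrees of freedom, with a two-sided 5% critical t of 4.30. The pooled contrast over 16 clusters has 16 − 2 = 14, with a critical t of 2.14.

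**Step 5: what is not affected in this way.**
- The specific objectives describe classification by IMCI alone and then by IMCI with pulse oximetry. The change on adding oximetry occurs within each PHC, so its interaction with format can be estimated even with PHC terms. Comparing that increment between formats still compares the same districts and NGOs.
- The descriptive analyses contain no PHC terms, and the cost section does not list PHC as a covariate. Costs are to be estimated in each country. Three of the four countries have one format only, so a within-country cost contrast exists in Mali alone.

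**The case against.** The strongest reply is that PHC is called a clustered variable and the same sentence turns to robust standard errors, so PHC may be meant only as the cluster identifier. The article is condensed, and the coding may be settled in a document not shown. This stands in part. Non-identification is conditional on PHC being a fixed covariate. That is the natural reading, because PHC heads the adjustment list and the clustering correction is named in addition, but it is not the only one. The reply does not remove the aliasing with NGO.

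A reader might go further and infer that the format comparison is impossible in every component, or that no information on e-IMCI remains. The protocol does not support that. The rank failure concerns the main effect in these logistic models. The oximetry-by-format increment is estimable, the descriptive and cost comparisons are confounded rather than non-estimable, and much of the process evaluation is qualitative.

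A reader might also treat user fees and training length as coinciding with format. They do not. The Discussion states that "health care for children under-5 is free for families in Niger and Burkina Faso but not in Mali and Guinea" (with listed disease exceptions), so each fee group contains both formats: 4 of 6 electronic and 4 of 10 paper research PHCs are in free-care countries. The 15-day training applies to Mali as a whole, which has one district of each format. Both can be adjusted for; the implementing NGO cannot.

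Finally, the main objective is the process of oximeter use, the design is described as non-comparative, and no sample size rests on format. Even with PHC terms, coefficients of child-level factors are unchanged whichever redundant column is dropped. This limits the weight of the point, but the comparison is still a stated aim.

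**Conclusion.** The point holds in a conditional form. If PHC is a fixed covariate, the main effects of e-IMCI versus paper and of rural/urban location are not identified in the associated-factor models (rank 16 before and after adding format). If PHC is only the cluster or a random intercept, the 6 versus 10 contrast can be computed, but it is completely aliased with one NGO and, outside Mali, with country (R² 0.733). Adjusting for country leaves 2 versus 2 PHCs, still one NGO and district against another. No adjustment of these data separates format from implementer.

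This rests on Table 1 as printed and on every PHC in a district using that district's format. It does not show that any difference seen would be spurious, or in which direction confounding would act; the documents give no figures for that.

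**What to change.** 1. In the associated-factor models, remove PHC from the fixed covariates. Use it only as the cluster, with robust standard errors and a small-sample correction for 16 clusters, or as a random intercept.
2. Add country as a fixed effect.
3. If the pooled e-IMCI versus paper difference is shown, present it together with the within-Mali Markala–Dioila difference (2 versus 2 research PHCs). Label both as exploratory and inseparable from NGO and district. Leaving out the P value or reporting only the Mali contrast is a matter of preference, not a requirement.
4. For the format comparison, replace the language of effect and added value with observed difference, in the objectives and the cost analysis.
5. Add this confounding to the limitations in the Discussion.

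The cost is a change of wording and model specification, and a weaker claim about e-IMCI. No new data are needed.
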